## Abstract

**Objectives:**

Mild cognitive impairment (MCI) affects about 11.4% of the elderly population in Hong Kong. This study mainly investigates the feasibility and efficacy of immersive virtual reality-based cognitive stimulation therapy (IVR-CST) on MCI, and the use of eye-tracking technology in studying treatment outcome.

**Hypothesis to be tested:**

1) Whether IVR-CST is a feasible intervention for the elderly with MCI. 2) Whether IVR-CST is efficacious (and more efficacious than conventional CST) in improving cognition. 3) Whether changes in eye movements across therapy and treatment outcome are associated.

**Design and subjects:**

An open-label, two-armed, assessor-blinded, randomized controlled trial will be conducted. Sixty-six elderly individuals with MCI will be recruited and randomly allocated to either the IVR-CST or the conventional CST group. Their cognition will be measured before and immediately after therapy and 4 weeks post-therapy.

**Interventions:**

A 14-session IVR-CST or conventional CST, with content adapted from the Chinese-translated manual of CST, will be carried out twice per week in groups of three to four individuals.

**Outcome measures and data analysis:**

The Hong Kong Montreal Cognitive Assessment and measures on executive functions/working memory will serve as primary outcomes. The within-subject (before and after therapy) and between-subject (IVR-CST vs. conventional CST) differences will be examined. Besides, eye movements during therapy in the IVR-CST group will be collected and its correlation with primary outcomes will be studied.

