### Participants

A total of 66 community-dwelling participants with MCI will be recruited from community centres for the elderly and Non-Governmental Organizations (NGOs) providing care services to elderly people with cognitive impairment in different districts in Hong Kong. The proposed sample size is calculated using G*power 3.1.9.4, based on a power estimate of 80% with α = .05, an effect size of d = 0.40 (with reference to the averaged effect size of 0.43 on global cognition, as reported in the latest Cochrane Review [9] on cognitive stimulation on PwD), and an attrition rate of 25%. The effect size of cognitive stimulation on PwD ranged from 0.3 to 1.32 [9], while an effect size of 0.564 was reported in adapted CST on MCI [16]. Also, the effect size of previous RCTs using VR on cognitive intervention of MCI ranged from 0.6 to 0.9 on measures of general cognition. Thus, an effect size estimate of 0.4 for the current proposal is considered relatively conservative. The attrition rates of previous VR studies on MCI are considered low (6–14%); thus, the estimated attrition rate of the current proposal is considered modest.

Inclusion criteria include: 1) elderly aged 60 years or above. 2) A score of 16–21 out of 30 in the Hong Kong Brief Cognitive Test [25], with upper and lower cutoff scores for MCI as suggested by the test. 3) ability to speak and comprehend Cantonese; 4) normal or corrected-to-normal vision and hearing; 5) absence of physical illness/disability to prevent them from IVR-CST participation; and 6) compatible with IVR exposure in the 10-minute IVR trial without major signs of cybersickness, based on the symptoms given in the Simulator Sickness Questionnaire [26]. Exclusion criteria include 1) concurrent participation in other clinical therapy trials; 2) incompatibility with IVR exposure such as complaints of nausea, headache, or other severe discomforts during trial use; 3) a diagnosis of dementia or other psychiatric/neurological diseases such as depression, stroke, brain trauma, Parkinson’s disease; 4) hearing/visual/upper limb impairments that hinder CST/IVR-CST participation; 5) prior CST treatment; 6) Use of medication for MCI/dementia, e.g., aducanumab. Screening will be done by a trained research assistant in a quiet room. Participants’ demographic information, medical and family history will be obtained.

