### Outcome measures and procedures

Primary outcomes: 1) The Hong Kong Montreal Cognitive Assessment (HK-MoCA; 27). It is a sensitive cognitive measure for MCI [27] and covers different cognitive domains, including visuo-spatial skills, executive functions, attention, memory, language, and orientation. The total score (out of 30) will be used to reflect global cognition; 2) Digit span forward and backward tasks, measures of working memory that predict progression from MCI to dementia [28]; 3) Verbal fluency of semantic category. Verbal fluency, which reflects semantic integrity, cognitive flexibility, and executive function, serves as a sensitive task in detecting MCI [29] and predicting conversion to dementia [30]. The number of items correctly produced in one minute in different semantic categories (animals, fruits, and transportation) will be tested.

Secondary outcomes: 1) Chinese version of the Modified Barthel Index [31], which assesses one’s level of independence in activities of daily living such as grooming, feeding, mobility, toileting, etc.; 2) The Hong Kong Lawton Instrumental Activities of Daily Living Scale [32], which evaluates the level of independency in performing community-living skills including cooking, household management, shopping, etc.

Feasibility outcome and users’ experience: Objective and quantifiable feasibility outcomes, including the number of adverse events and technical issues that occurred during intervention, and the level of adherence (actual duration and number of sessions conducted vs. scheduled) to the intervention protocol of both treatment groups, will be measured. Participants of the IVR-CST group will also attend a 20-minute semi-structured interview conducted post-therapy on topics including levels of comfort, presence of adverse effects such as cybersickness, and impact of therapy on daily functions.

Eye-tracking data obtained from the IVR-CST group will serve as an exploratory outcome. In each of the sessions, areas of interest (AOI) of the stimuli presented will be identified. For example, the childhood snacks or toys presented in the themed session ‘Childhood’ will be regarded as AOI. Parameters, including the number of fixations, duration of fixation, and number of revisits on the AOI generated by each participant, will be recorded in the HMD.

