### Data analysis

Primary and secondary outcomes will be scored by a trained research assistant who is not involved in the assessment. To further reduce observer bias, a random code will be given to the scoring forms and audio-recording so that the research assistant will be blind to the identity of the participant, the experimental group assigned, and the timepoint of assessment. A linear fixed-effect model will be used to evaluate the participants’ performance in the outcome measures, as this statistical model is better in handling repeated observations, missing data, and individual variability [33]. Both time points (week 1/9/13) and conditions (IVR-CST vs. conventional CST) will serve as fixed factors, and scores of primary/secondary outcomes as dependent variables. Participants’ characteristics, such as age, baseline cognitive performance, and education, will be included in the model as covariates. Any significant main effects or interactions will be investigated via post-hoc analyses. Measurements concerning feasibility and user experience will be evaluated descriptively. In addition, a narrative summary of responses collected during the post-therapy interview will be reported.

For exploratory outcome, a 5-minute sample will be extracted from each participant and session from the IVR-CST group. To study possible changes in eye movement across sessions, the aforementioned eye-tracking parameters, including number of fixations, duration of fixation, and number of revisits on the AOI generated by each participant, will be evaluated by linear fixed-effect models as dependent variables, with session number as a fixed factor. Any significant main effects will be followed by post-hoc analyses. To investigate the possible associations between eye movement and treatment outcome, the correlation between the averaged difference in number and duration of eye fixations of each participant in the first and last three IVR-CST sessions and the difference score of HK-MoCA before and immediately after therapy will be analysed. If the correlation reaches statistical significance, multiple regression will be conducted, with the eye-tracking parameters as predictors, while the difference score of HK-MoCA pre/post therapy will serve as the predicted variable.

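### Three co-equal primary outcomes, two follow-ups and several unranked effects are set against a sample size for one test, and nothing says which result decides superiority over conventional CST

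*Protocol article*

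**What the plan says.** All references are to the protocol article.

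- **Abstract, Outcome measures and data analysis:** "The Hong Kong Montreal Cognitive Assessment and measures on executive functions/working memory will serve as primary outcomes". The same paragraph plans both before-after and between-arm comparisons and ranks neither.
- **Outcome measures and procedures:** three numbered primary outcomes: HK-MoCA total; digit span forward and backward; semantic verbal fluency. On fluency: "The number of items correctly produced in one minute in different semantic categories (animals, fruits, and transportation) will be tested". Whether the two digit spans, or the three categories, are combined is not stated.
- **Assessment and treatment schedule:** assessments at weeks 1, 9 and 13. Neither follow-up is named as primary.
- **Data analysis:** time and condition are fixed factors for every primary and secondary outcome. Then: "Any significant main effects or interactions will be investigated via post-hoc analyses".
- **Participants:** "A total of 66 community-dwelling participants with MCI will be recruited". The calculation is "based on a power estimate of 80% with α = .05, an effect size of d = 0.40", chosen "with reference to the averaged effect size of 0.43 on global cognition", with 25% attrition.
- **Aims and hypotheses:** whether IVR-CST is efficacious, and whether it is more efficacious than conventional CST, are separate questions. Both refer only to cognition.

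**The concern.** The plan gives several outcomes equal primary standing, at two follow-ups, with more than one model effect each, but sizes the trial as if one test would be made. The superiority question is therefore tied to no particular score, time or contrast, and a reader of the results could not tell which finding was meant to settle it.

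Two things are at stake. First, if a favourable result on any primary score is taken as the answer, the chance of a false claim of superiority exceeds .05. Second, a later adjustment for several primary outcomes would not fit the sizing paragraph, which leaves no room for a smaller alpha.

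The content of the therapy sharpens this. The session 9 example in Table 1 practises semantic verbal fluency, with IVR cues in one arm only. A difference on fluency alone could partly reflect task practice, yet would rank equally with a difference in global cognition. The Discussion says the efficacy findings will inform whether to scale up.

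**Working it through.** **1. Inputs from the article.** Alpha .05, power 80%, d = 0.40, attrition 25%, N = 66 (Participants); 1:1 allocation (Randomization); three numbered primary outcomes; follow-ups at weeks 9 and 13.

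**2. Reproducing 66.** The article does not name the test or its sidedness; two-sided is assumed.
- Paired t-test, d = 0.40: 51.01, so 52 evaluable.
- Two-group by two-time interaction, f = 0.20, assumed within-person correlation .5: noncentrality 0.20² × 52 × 2 / (1 − 0.5) = 8.32 and power 80.7%, so again 52.
- 52 × 1.25 = 65, or 66 for equal arms. (52 / 0.75 would give 70.)
- Independent two-group t-test, d = 0.40: 99.08 per arm, so 100 per arm and 200 evaluable.

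So 66 is recovered as one paired or interaction-type test at unadjusted .05, with attrition added by multiplication.

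**3. Counting scores.** Three if digit span is combined and fluency summed; four if digit span forward and backward are separate; six if the fluency categories are also separate.

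**4. Simple bound, one test per score.** With k independent tests at .05, the chance of at least one false positive is 1 − 0.95^k.

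| k | independent | correlation .5 | correlation .7 |
|---|---|---|---|
| 3 | 14.3% | 12.6% | 10.9% |
| 4 | 18.5% | 15.6% | 13.1% |
| 6 | 26.5% | 20.7% | 16.4% |

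Eight independent tests (four scores at two follow-ups) would give 33.7%, but that treats two measurements on the same person as independent. Allowing for that correlation gives about 30-32% with uncorrelated outcomes and 25-27% at outcome correlation .5.

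**5. Simulation closer to the planned model.** Two arms, three times, N = 66, complete data, within-person correlation .6, no covariates, no true effect. Entries are the chance of at least one significant between-arm result at .05, for outcome correlations 0 / .5 / .7.

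| What counts as a positive result | 3 scores | 4 scores | 6 scores |
|---|---|---|---|
| Week 9 or 13 contrast, only after a significant interaction | 12.0 / 10.7 / 9.6% | 15.2 / 13.4 / 11.1% | 22.6 / 17.7 / 14.5% |
| Interaction alone | 14.2 / 12.6 / 11.2% | 18.2 / 16.1 / 13.1% | 26.9 / 20.7 / 16.9% |
| Week 9 or 13 contrast, no gate | 24.9 / 21.9 / 19.4% | 31.2 / 27.2 / 22.2% | 43.7 / 35.0 / 28.5% |
| Condition or interaction | 26.7 / 23.6 / 21.0% | 33.5 / 29.2 / 24.0% | 45.9 / 37.0 / 30.9% |

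For three or four scores the range is 9.6% to 33.5%. The time main effect is left out because it carries no between-arm information.

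**6. Keeping four primary scores and adjusting.** Bonferroni gives .05 / 4 = .0125 each. On the step 2 calculation, power per score at 52 evaluable falls from about 81% to about 62%. Restoring 80% needs 73-74 evaluable (92-93 after × 1.25).

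**7. Between-arm power at the planned size.** A plain two-group t-test at d = 0.40 has about 29% power with 52 evaluable (26 per arm) and about 36% with 66 (33 per arm).

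**The case against.** The strongest reply is that only a condensed article is at hand, and that per-test significance levels and multiplicity methods usually sit in an analysis plan or full protocol. That stands: the absence of an adjustment method is not the finding. The finding rests on what the article itself fixes, namely co-equal primary outcomes and unranked contrasts beside a single-test sample size.

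Three stronger readings are tempting and not supported:

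- *That the trial's error rate is 16-34%.* The article states no success rule, neither any-one nor all-must-succeed, and gives .05 only in the sizing sentence. It also claims no family-wise rate. Every percentage above is conditional on an any-one-wins reading at .05.
- *That there are at least four primary outcomes.* Three are numbered; four or six needs an assumption about splitting them.
- *That any significant effect would support superiority.* A time effect bears on whether participants improve, not on IVR-CST against conventional CST. Post-hoc contrasts also follow a significant main effect or interaction, so they are not free-standing tests; gating on the interaction lowers the figure for four scores to about 11-15%.

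It is also fair to say that feasibility is the first research question and that the Discussion concedes the small sample reduces power and calls the findings initial. That tempers the consequences. It does not remove the superiority question, which the article poses explicitly.

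**Conclusion.** The point holds in conditional form. The article names three co-equal primary outcomes (three to six scores), two follow-ups and several unranked contrasts and effects, sizes the trial for one test on global cognition, and does not say which result decides superiority.

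If any significant condition effect or interaction on a primary score were read as success at .05, the false-positive chance would be roughly 10-34% for three or four scores and up to about 46% for six analysed separately. This rests on the any-one-wins reading, outcome correlations of 0 to .7, within-person correlation .6 and complete data, none of which the article gives. Every scenario tried is at least about twice .05, so the direction does not depend on the choice among them.

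**What to change.** Name one primary contrast that matches the outcome used for sizing: the between-arm difference in change in HK-MoCA total from baseline to week 9, two-sided .05. This is one defensible choice. It fits the article, which already uses the HK-MoCA change from before to immediately after therapy as the treatment outcome in the eye-tracking analysis.

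Make digit span, verbal fluency (summed over the three categories) and all week-13 results secondary. Report them as estimates with 95% confidence intervals, Holm-adjusted if an efficacy claim is drawn from them.

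The cost is wording in the protocol and the registry entry. The downside is that a positive result on fluency or digit span alone becomes supportive only.

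This change does not establish that 66 is adequate. The sizing paragraph should separately state the test and correlation assumed, and the power for the between-arm contrast.

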**Expected results:**

Positive changes in cognition are expected after therapy in both treatment groups, which may be maintained four weeks post-therapy.

**Trial registration:**

ClinicalTrials.gov ID: NCT06838494

## Introduction

MCI, a mild neurocognitive disorder as defined by the Diagnostic and Statistical Manual Fifth Edition (DSM-5) and Word Health Organization – International Classification of Diseases (WHO-ICD), affects various cognitive domains such as memory, attention, language, executive functions, and visual-spatial processing but yet the individual’s functions in daily activities are relatively normal. MCI is regarded as a heterogeneous condition between normal aging and dementia [1]. The prevalence of MCI, which may vary across countries, cultures, and age, is reported to range from 3% to 42% [2]. Whereas in Hong Kong, the incidence rate is about 114.4 cases per 1000 person-years [3]. Individuals with MCI have a much higher chance of developing dementia when compared to those without MCI. It is estimated that 46% of the MCI population will convert to dementia when compared to a 3% chance of those without MCI [4]. Much effort has been devoted to improving the early identification and management of MCI. Most of the intervention studies investigated remedies that have been tested in the dementia population. Pharmacological interventions studied the use of cholinesterase inhibitors, galantamine, and donepezil, while nonpharmacological interventions investigated the effects of behavioral programs (e.g., physical or cognitive exercises) and non-invasive brain stimulation (e.g., repetitive transcranial magnetic stimulation) on cognitive functions of people with MCI. Findings from systematic reviews revealed that pharmacological interventions are not beneficial to cognition [1,5], and a small but uncertain cognitive benefit has been found in behavioral treatment [5,6]. The conclusion on the effects of non-invasive brain stimulation has remained inconclusive [7]. Further research on non-pharmacological interventions with high-quality randomized controlled trials (RCTs) is encouraged.

### Cognitive stimulation therapy: A potentially beneficial intervention for MCI?

Despite the lack of official guidelines for treatment on MCI, recommendations from institutes/organizations on the management of dementia may shed light on directions for future development. Non-pharmacological interventions are considered the key component to managing the disease. Among the three approaches to cognitive intervention on dementia defined by Clare and Woods, cognitive stimulation, as defined as “engagement in a range of activities and discussions (usually in a group) aimed at general enhancement of cognitive and social functioning”, has been regarded as beneficial to people with dementia (PwD) [8]. Three key aspects of cognitive stimulation, namely ‘generalized cognitive exercise’, ‘social interaction’, and ‘social support’, are suggested to constitute the underlying mechanisms leading to treatment success [9]. A recent Cochrane Review concluded that cognitive stimulation has a small and short-term benefit (a standard mean difference of 0.43 s.d.) on the general cognitive functioning of people with mild-to-moderate dementia [9]. Contrastively, the other two approaches, namely cognitive training, which involves drilling of decontextualized and standardized tasks tapping certain cognitive processes, and cognitive rehabilitation, which refers to use of strategies to accomplish daily functions, are much less effective (or even not effective when cognitive training is considered) in promoting cognition of PwD [10]. Among different cognitive stimulation programs, CST, an intervention with high-quality evidence based on RCTs, is considered a more popular and influential group intervention protocol with much research support from a worldwide perspective [11]. CST, a 14-session group-based activity program for mild-to-moderate PwD, is conducted by one or two trained facilitators (who can be a health care professional or a volunteer) and a group size of five to six PwD at most. A total of 18 key principles in implementing CST, e.g., mental stimulation, stimulating language and executive functioning, and building/strengthening relationships, are emphasized in facilitator training and CST manuals. In each session, different themed activities such as childhood, current affairs, and physical/word/number games are carried out to provide generalized cognitive exercise to the participants. Furthermore, aspects of social interaction and support are achieved via frequent and continual interpersonal communication in a group context throughout therapy. CST has been recommended by the National Institute for Health and Care Excellence (NICE) of the United Kingdom government [10] and the World Alzheimer Report of ADI (2011) for PwD. CST has been available in at least 34 countries, while in a local context, a translated manual in Chinese [12], a pilot study on conventional CST [13], and a preliminary virtual individual CST (vCST) study delivered via Zoom have been conducted [14] with positive changes in cognition demonstrated in both studies. In view of the success CST has brought to PwD, it is reasonable to hypothesize that individuals with MCI may potentially benefit from it. Since the presenting symptoms and neuropathology of MCI and dementia are highly similar [15], the mechanisms accounting for the cognitive improvements induced by CST would likely take place in the MCI population. In fact, an RCT, based on adapted CST activities, has demonstrated positive effects on global cognition (with a medium effect size of d=0.564) in terms of the Spanish version of MMSE [16]. Positive as it may seem, one may question if the level of difficulty of the themed activities offered in CST may be too easy or not mentally stimulating to the MCI population. The present study intends to provide a solution via the application of immersive virtual reality (IVR) – a novel and safe means to create a stimulating and novel therapy context, and to take advantage of the technological advancement IVR offers in monitoring of users’ experience to facilitate treatment delivery and enhance treatment outcome.

### IVR-CST: Justifications and potential benefits for MCI

VR has been applied in health care and therapy delivery for more than 20 years. It aims to create an artificial environment to replace real-world surroundings via equipment such as a head-mounted display (HMD), headphones with music/sound, and devices for manipulation/navigation in the virtual environment. The application of VR/IVR in MCI/dementia therapy has been emerging. A recent systematic review studying VR-based neuropsychological interventions reported a moderate effect and a large effect on global cognition (g = 0.30) and executive functions (g = 0.60) of older adults with MCI (mean age about 70 years), respectively [17]. More specifically, another review [18] compared the efficacy of VR-based cognitive rehabilitation with those without VR, in which IVR was used in one of the studies [19]. VR-based intervention was at least as effective (or more effective than conventional treatment without VR in some of the outcomes) as conventional cognitive rehabilitation on the MCI population [18]. In addition, good user acceptability, minimal cybersickness/adverse events, and preference for IVR have provided further incentives and support to future research with well-designed RCTs [20]. As a matter of fact, a closer look at the studies included in the review on VR may shed light on issues related to study design and theoretical considerations. Firstly, regarding the nature of intervention, most of the studies belonged to cognitive rehabilitation, an intervention approach less recommended by NICE for PwD. In contrast, the efficacy of VR-based cognitive stimulation has rarely been studied, except for pilot studies [21]. Secondly, little was known about the theoretical basis for the selection of treatment content/protocol. Most of the studies argued that multisensory experience and a more focused environment rendered by IVR might promote treatment success. Little consideration/attention was made regarding how the treatment per se, and its underlying mechanism, may improve the cognitive functions of the participants. If IVR is applied to treatment protocols with uncertain treatment efficacy/mechanism accounting for treatment success, its power in promoting treatment outcomes will be undermined. To address the above issues, our proposed study aims to incorporate IVR in CST delivery and investigate its efficacy in improving the cognition of people with MCI with the following justifications. Firstly, CST is a well-developed and evidence-based program; its implementation in the local MCI population is culturally appropriate and ecologically valid. Based on a case series conducted by the first author, the use of IVR-CST yielded positive results in terms of users’ acceptability, compliance, and some improvements in communication among PwD with visual impairment [22]. Secondly, during IVR-CST, users will immerse themselves in a novel virtual environment and engage in a series of cognitively stimulating activities, which are concurrent with the principles of CST, such as mental stimulation, being fun, and choice. Thirdly, the immersive environment may enable the participants to focus and pay better attention to the treatment stimuli. Last but not least, social participation and connectedness, which are important principles of CST, are readily provided during group interactions.
